#### Data editing

Data editing will be done in two phases i-e field editing and office editing. Field editing will be done by the field supervisors where they will check each questionnaire filled by HVRA on the hard copy of questionnaire every week. These filed supervisors will hand over forms to quality assurance officer on a weekly basis who will bring forms to AKU data management unit and will edit forms in the central office of AKU.

#### Data entry and cleaning

Two data entry operators will enter the data into a data entry program in parallel. The data entry program will be designed using EPI data. Data entered will be compared for entry errors and the identified errors will be corrected. 10% of the records will be randomly chosen from the database and will be validated against the questionnaire data. If there is more than 0.3% discrepancy between the two, data entry will be done again. The hard copy forms will be kept in the secure location for possible once the double data entry is completed.

#### Data analysis

Quantitative data will be double-entered in EPI-Data software. The primary outcome of analysis will be anemia which has been defined in agreement with WHO definitions for anemia, which are Hb < 12.0 g/dl or Hct < 36% for non-pregnant women [22]. Frequencies and percentages will be calculated for qualitative variables like working status, education level, and employment status, the occupation of the woman and her husband, any pre-existing medical conditions. Means and standard deviations or median with inter-quartile range whatever will be appropriate for the continuous variables including current age of the woman, age at the time of marriage, parity, number of alive children and number of prior sons etc. will be generated for all participants.

Univariate analysis will be conducted by computing unadjusted odds ratio (OR) and their 95% confidence intervals to compare the anemic and non-anemic women with respect to all the possible biological and socio-demographic factors. The appropriate test for example chi-square will be used to assess the association between variables. Multicollinearity between independent variables will be assessed. The variables for which *p*-value turns out to be less than 0.25 will be included in the multivariable analysis. In the multivariable analysis, multiple logistic regressions will be used to compute the adjusted odds ratio with 95% confidence intervals. During this analysis interaction between the variables will be assessed. This analysis will also be helpful in identifying the potential confounders related to the study. Data will be analyzed using SPSS version 19.0 version.

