### Study objectives

#### The objectives of this study are two-fold

The objective for the qualitative phase includes:To explore the knowledge and perceptions of women, their husbands and health care providers about anemia, its possible causes, how does it impact maternal and child health and what could be done to address this crucial problem in the district.The objective for the quantitative phase include:To study the sociodemographic factors associated with anemia among women of the reproductive age group in Thatta District.To study the biological factors associated with anemia among women of the reproductive age group in Thatta District.To study the sociodemographic factors associated with anemia among men in Thatta District.

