#### Quantitative study

In this phase of the study, a cross-sectional study will be conducted by using a structured and validated questionnaire to collect the data for this study. The questionnaire has been designed by taking validated questions form DHS (Demographic health survey) and Pakistan demographic health survey 2012–2013. The questionnaire will be consisting of socio-demographic and fertility-related information (age, marital status, parity, educational level, working status, socioeconomic status, religion, and place of residence) about the participants. This will also include all the related information for knowledge of contraceptives and its usage. Anthropometric measurements (weight, height, body mass index, waist circumference, hip circumference, mid-upper arm circumference, and head circumference.) will be conducted from enrolled women. Moreover, a 24-h dietary recall will be undertaken from enrolled women by using a 24-h dietary recall questionnaire which had also been used in the main WF trail for pregnant women in the same catchment area. This dietary recall questionnaire will help to assess the die consumed by women in district Thatta. In addition, socio-demographic characteristics of the enrolled husbands will be also collected on a separate one-page questionnaire.

The questionnaire will be pretested in the area having similar characteristics as that of the study site on the participants different from the study. The flow of questions and comprehensibility will be assessed during pre-testing the questionnaire. Refinement of the questionnaire will be done and refresher training of data collectors will be conducted by the Principal investigator and senior research coordinator of the study. This will be followed by actual and real administration of the questionnaire in the field.

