All biological sample being collected from enrolled women will be transferred from Thatta collection points to the main Aga Khan Hospital Karachi Pakistan under the required cold chain. The main laboratory of the Aga Khan University Hospital Karachi is well equipped and has the capacity to analyze the blood samples for the proposed markers and investigations such as complete blood count (CBC), serum iron, folic acid, Erythrocyte Sedimentation Rate (ESR), C-Reactive Protein Test (CRP), B12, ferritin, hemoglobinopathies, the presence of malarial parasite and stool analysis for worm infestation. Biological samples will be stored and analyzed in the Aga Khan Hospital laboratory by qualified personnel. The remaining samples will be destroyed as per AKU laboratory policy at the end of the study mainly after the analysis is done and reports are generated. Once the laboratory reports are generated, HVRAs will hand over reports to the women and will advise and facilitate them to contact local health care provider for getting health services free of cost from district hospital if required.

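### Socio-demographic and biological factors share one screen and one adjusted analysis, so the adjusted odds ratios for socio-demographic factors will usually leave out the part that acts through the biomarkers

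*Protocol article*

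**What the plan says.** In the Protocol article, the objectives section lists two separate quantitative objectives for women: "To study the sociodemographic factors associated with anemia among women of the reproductive age group in Thatta District" and "To study the biological factors associated with anemia among women of the reproductive age group in Thatta District".

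The quantitative Data analysis section does not carry that separation forward. It plans unadjusted ORs with 95% confidence intervals "to compare the anemic and non-anemic women with respect to all the possible biological and socio-demographic factors". A variable whose p-value "turns out to be less than 0.25 will be included in the multivariable analysis", whatever kind of factor it is. Then "multiple logistic regressions will be used to compute the adjusted odds ratio with 95% confidence intervals". Multicollinearity and interaction are to be checked. On confounding the section says only: "This analysis will also be helpful in identifying the potential confounders related to the study". It gives no model per objective, no blocks or entry order, and no distinction between a mediator and a confounder.

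The candidate variables come from two sources. The questionnaire (Quantitative study section) supplies "socio-demographic and fertility-related information (age, marital status, parity, educational level, working status, socioeconomic status, religion, and place of residence". The laboratory work (Biological sample collection section) supplies "complete blood count (CBC), serum iron, folic acid, Erythrocyte Sedimentation Rate (ESR), C-Reactive Protein Test (CRP), B12, ferritin, hemoglobinopathies", along with malaria parasites and stool analysis for worms.

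**The concern.** The measured biomarkers plausibly lie between social position and anemia. A woman with little schooling or few resources may become anemic because her iron or folate is low or because she carries worms. If ferritin, folate and worm infestation are in the model, the OR for education or socioeconomic status compares women with the same iron, folate and worm status. That is a direct association, net of the mechanism. The first objective, read plainly, asks for the association as a whole.

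The screen does not protect against this, because a biomarker close to the outcome is the kind of variable that passes p below 0.25. Nor does looking for confounders in the fitted analysis: a mediator and a confounder can shift an OR in the same way, and the data alone do not tell them apart.

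The Discussion says the results should guide interventions and policy. A weak adjusted OR for a socio-demographic factor, produced only by holding iron status fixed, could be read as evidence that the factor matters little.

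**Working it through.** The plan states no figure for any adjusted OR, so there is nothing of its own to reproduce. The check has two parts: what the rule does as written, and how far an OR could move.

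**1. The rule as written.** Two objectives feed one pooled list of candidates. One threshold, blind to type of factor, decides entry, and one multivariable analysis yields the adjusted ORs. If the rule is followed literally, any biomarker that passes stands beside the socio-demographic factors.

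**2. Inputs.** From the documents: 150 women, and anemia prevalence from 21% to 75% (Sample size section). The documents do not say how common a biomarker abnormality is by social group, or how strongly it relates to anemia. All such values below are assumptions.

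**3. Hand example, full mediation.** Assume iron deficiency in 35% of higher-status and 65% of lower-status women, anemia in 35% without and 75% with deficiency, and no other path.

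- Higher status: 0.65 × 0.35 + 0.35 × 0.75 = 0.49
- Lower status: 0.35 × 0.35 + 0.65 × 0.75 = 0.61
- OR without the biomarker: (0.61/0.39) / (0.49/0.51) = 1.63
- OR with the biomarker: 1.00, by construction

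Now add a direct OR of 1.3. Anemia in lower-status women becomes 0.412 without and 0.796 with deficiency, so overall 0.35 × 0.412 + 0.65 × 0.796 = 0.661. The OR is (0.661/0.339) / (0.49/0.51) = 2.03 without the biomarker and 1.30 with it. The assumed mediator is strong: its own OR is (0.75/0.25) / (0.35/0.65) = 5.6.

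**4. A range of assumptions.** Let X be a binary socio-demographic factor (50% exposed) and M a binary biomarker, with logit P(anemia) = a + b·X + c·M and a set so that 50% are anemic. The OR for X without M comes from averaging over M within each level of X. The OR with M is exp(b).

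| M present, X = 1 vs X = 0 | OR for M | Direct OR for X | OR without M | OR with M |
|---|---|---|---|---|
| 50% vs 40% | 2 | 1.5 | 1.59 | 1.50 |
| 60% vs 40% | 4 | 2.0 | 2.43 | 2.00 |
| 70% vs 30% | 4 | 1.5 | 2.47 | 1.50 |
| 70% vs 30% | 8 | 1.5 | 3.00 | 1.50 |
| 70% vs 30% | 4 | 1.0 | 1.71 | 1.00 |
| 70% vs 30% | 4 | 0.5 | 0.91 | 0.50 |
| 50% vs 50% | 8 | 2.0 | 1.71 | 2.00 |

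For the third row, anemia is 0.611 in exposed and 0.389 in unexposed women, so (0.611/0.389) / (0.389/0.611) = 2.47.

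The last two rows are the exceptions. Where the direct and mediated paths oppose each other, adjustment moves the OR away from 1 (medians of 0.92 and 0.49 in simulated studies). Where a strong biomarker is unrelated to the factor, non-collapsibility alone moves it from 1.71 to 2.00.

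**5. Simulation at n = 150** (1,000 studies per setting). Biomarkers with an OR of 4 to 8 passed the p < 0.25 screen in 98% to 100% of studies. In the third-row setting, power to detect the socio-demographic factor at the 5% level was:

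| Anemia prevalence | Without M | With M |
|---|---|---|
| 21% | 58% | 14% |
| 50% | 76% | 18% |
| 75% | 63% | 16% |

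**The case against.** **The section never says there is one model.** This is true. It gives no model count, and model-building order is detail that a condensed article may leave to a fuller plan. A single model is the natural reading of a shared screen and a single entry rule, not literal text. The point still does not depend on missing detail: the entry rule is stated, is mandatory, and makes no exception by type of factor.

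**Unadjusted ORs will be reported for every factor.** They will, so the crude association stays visible, and a reader should not infer that the study would simply report poverty or education as unrelated to anemia. The mitigation is partial. A crude OR for education also carries age, parity and socioeconomic status, and so does not replace an adjusted total association.

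**The mediation is the reviewer's structure, not the protocol's.** In part. The Background names iron and folic acid deficiency, malaria and hookworm as possible reasons for higher risk. It then lists socio-demographic factors beside nutritional deficiencies, without saying that the former act through the latter. The path is plausible but is not asserted there.

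**Not every biomarker need pass the screen.** Agreed. The pass rates above apply to ORs of 4 to 8. The documents give no prevalence or effect for malaria, worms or B12 in this sample.

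**Red-cell indices.** A reader might infer that hemoglobin, hematocrit or MCV will be entered as predictors, because the blood count is among the investigations. The documents do not support that. Hemoglobin and hematocrit define the outcome, no index is named as a predictor, and the Discussion speaks of identifying the type of anemia. One clarifying sentence is enough.

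**Conclusion.** The concern holds in limited form. Two separate objectives share one screen and one adjusted analysis, and the stated entry rule lets likely mediators into the model from which socio-demographic ORs are read. On the natural reading, those ORs describe associations net of the biomarkers, which is a different question from the first objective.

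It is tempting to conclude that the adjusted ORs are always driven toward 1. That is not supported. Attenuation needs a biomarker that passes the screen and mediates in the same direction as any direct effect. It is the usual result but not a certain one.

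The size cannot be derived from the documents. Under the assumptions shown, it runs from negligible (1.59 to 1.50) to substantial (2.47 to 1.50) to complete (1.63 to 1.00). The change should be made before the analysis, but the fault does not invalidate the study: the data to be collected are those the correct analysis needs.

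**What to change.** In the quantitative Data analysis section, replace the single pooled path with one path per objective:

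- **Socio-demographic objective.** Report adjusted ORs from a model with socio-demographic and reproductive factors only and no biomarkers.
- **Biological objective.** Report ORs for the biological factors, adjusted for socio-demographic confounders named in advance.
- **Any model holding both.** Label its socio-demographic ORs as direct associations, net of the biomarkers, and do not use them as the answer to the first objective.
- **Minor clarification.** State that hemoglobin, hematocrit and red-cell indices serve to define or type the anemia and are not predictors.

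The cost is a revised paragraph, a short list of confounders fixed beforehand, and a few extra model runs, since the biological factors may need more than one model. No new data, participants or laboratory work are needed.

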In addition, maternal and newborn health registry (MNHR) has been maintained in 9 Union councils (UCs) of district Thatta, which documents birth outcomes and provide population-based rates of stillbirth, neonatal and maternal deaths [11, 12]. Recent MNHR data of 2017 also shows that 15.2% of pregnant women in these UCs are found to be severely anemic (Hb < 8 g. /dl), and 39.2% have been found as moderately anemic (Hb 8–10 g/dl) (Unpublished data). MNHR data also showed that severe anemia is more common in Pakistan as compared to India (0.2%) (unpublished data). Although both the India and Pakistan sites are quite similar in terms of their socio-demographic characteristics, there are huge differences in the proportion of women with very low Hb levels. Nevertheless, in both countries, the underlying cause of anemia needs to be explored across the range of socio-cultural and biological factors. Looking at these differences in the same area and with neighboring countries, it is highly essential to explore the factors of anemia among women of reproductive age group. In addition, through this study we will also explore the perceptions of women, their husbands and health care providers about anemia, its possible causes, how does it impact maternal and child health and what could be done to address this crucial problem in the district.

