#### Sample size and sampling method

A minimum sample of 150 women will be required in order to achieve a power of 80% at 5% level of significance, keeping proportion of anemia among women of reproductive age group from 21 to 75%, anticipated proportion of various risk factors in the range of 20 to 75% among anemic group and 20 to 82% among non-anemic group. In addition to 150 women, their spouses will also be included thus making a total of 300 participants to achieve the objective of quantitating phase of the proposed study. A probability simple random sampling technique will be used to select the participants. A sampling frame will be generated from existing data of WF participants and participants will be identified randomly from the given list by a third person mainly the data manager of MNHR.

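### Factors are analysed only against anemia yes/no although hemoglobin is measured in g/dl; a companion regression on hemoglobin would be a cheap gain in efficiency

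*Protocol article*

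**What the plan says.** The Data analysis section of Phase 2 in the protocol article fixes the outcome: "The primary outcome of analysis will be anemia which has been defined in agreement with WHO definitions for anemia", namely "Hb < 12.0 g/dl or Hct < 36% for non-pregnant women". Unadjusted odds ratios are computed first, "to compare the anemic and non-anemic women with respect to all the possible biological and socio-demographic factors". Variables with p below 0.25 go forward, and then "multiple logistic regressions will be used to compute the adjusted odds ratio with 95% confidence intervals". The Abstract describes the same logistic analysis.

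The Data collection method section has Hb obtained as a number in two ways, from a complete blood count on venous blood and from a HemoCue device. The only use it gives for Hb on its own scale is to compare the two methods.

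The Sample size section says: "A minimum sample of 150 women will be required in order to achieve a power of 80% at 5% level of significance". It assumes a prevalence given as "keeping proportion of anemia among women of reproductive age group from 21 to 75"%.

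The Background compares Pakistan with India and says that "there are huge differences in the proportion of women with very low Hb levels". It reports 15.2% of pregnant women below 8 g/dl in the registry area, against 0.2% in India. The Study objectives speak of factors associated with anemia and do not mention severity.

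**The concern.** Reducing a measured value to above or below a cut discards how far each woman lies from it. A woman at 11.9 g/dl and one at 7.0 g/dl count the same, as do women at 12.1 and 14.0.

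Two things are at stake. The first is power. The sample is fixed at 150 women, and the analysis is meant to screen many biological and socio-demographic factors and their interactions. The smaller outcome group is about 32 anemic women at 21% prevalence (150 × 0.21 = 31.5) or about 38 non-anemic women at 75% (150 × 0.25 = 37.5). A real association is easily missed with so few.

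The second is relevance. The Background points to the low end of the Hb scale, and the planned outcome does not separate that end from mild anemia.

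**Working it through.** **The plan's own figure.** The 150 cannot be tied to one calculation, because the Sample size section gives only ranges: "anticipated proportion of various risk factors in the range of 20 to 75% among anemic group and 20 to 82% among non-anemic group". A two-sided 5% comparison of two proportions, with the group ratio set by prevalence 21%, 50% and 75%, gives:

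- 75% of anemic against 82% of non-anemic women exposed: power 15.7%, 17.9% and 12.5% with 150 women; total needed 1,581, 1,080 and 1,471.
- 20% against 82%: total needed 29, 18 and 23.
- 75% against 20%: total needed 33, 24 and 31.

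The figure of 150 lies between these extremes. The check below therefore takes 150 women and the prevalence range as given.

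**Efficiency of the cut.** Assume that Hb is normal, that a factor shifts it by a small uniform amount, and that the outcome is a pure Hb cut. The efficiency of the yes/no outcome relative to Hb itself, at prevalence p, is φ(z_p)² / [p(1 − p)], where z_p is the normal quantile of p and φ the normal density.

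| Prevalence | φ(z_p) | φ² | p(1 − p) | Efficiency | Loss | 150 × efficiency |
|---|---|---|---|---|---|---|
| 21% | 0.288 | 0.0831 | 0.1659 | 0.501 | 49.9% | 75 |
| 50% | 0.399 | 0.1592 | 0.2500 | 0.637 | 36.3% | 95 |
| 75% | 0.318 | 0.1010 | 0.1875 | 0.539 | 46.1% | 81 |

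**What this means for power.** Take a factor present in half the women. The shift that an analysis of Hb detects with 80% power at n = 150 is √(4/150) × (1.960 + 0.842) = 0.457 SD. With the cut placed to give each overall prevalence:

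| Prevalence | Anemic, two exposure groups | Power of yes/no analysis | Total women for 80% |
|---|---|---|---|
| 21% | 27.5% v 14.5% | 49% | 310 |
| 50% | 59.0% v 41.0% | 60% | 238 |
| 75% | 82.1% v 67.9% | 53% | 286 |

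A simulation (4,000 runs per case) agrees. It assumed an Hb SD of 1.5 g/dl, so the shift is 0.457 × 1.5 = 0.69 g/dl. Linear regression had power 0.79 to 0.80; logistic regression had 0.512, 0.593 and 0.543 at the three prevalences. The SD only converts the shift to g/dl.

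**Dependence on the shape of Hb.** For density f, cut c and standard deviation SD, the efficiency is f(c)² SD² / [p(1 − p)]. The article gives neither a distribution nor an SD, so the range is:

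| Assumed shape | Loss at 21% | at 50% | at 75% |
|---|---|---|---|
| Normal | 49.9% | 36.3% | 46.1% |
| Logistic | 45.4% | 17.8% | 38.3% |
| t, 5 df | 38.8% | 3.9% | 29.9% |
| Skew-normal, skewness −0.45 | 61.3% | 33.4% | 28.6% |
| Skew-normal, skewness −0.78 | 68.0% | 35.7% | 2.0% |
| Left-skewed Gumbel, skewness −1.14 | 65.6% | 21.0% | −5.4% |

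In the last cell the cut is slightly the more efficient. The gain from Hb is therefore likely but not guaranteed, and it is least certain with strong left skew and high prevalence.

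**The case against.** The strongest reply is that the plan answers its own question. The objectives ask about factors associated with anemia; WHO-defined anemia with adjusted odds ratios estimates exactly that. The efficiency figure concerns a different target, a shift in mean Hb. This stands. A reader might infer that the logistic model is wrong, or that linear regression should replace it as the main analysis; the documents do not support either.

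A reader might also infer that about 15% of the enrolled women will be severely anemic. The registry figure is for pregnant women, and this study excludes them. The article gives no severity figure for non-pregnant women, so the size of the low tail is unknown.

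It is equally fair to say that a mean difference does not isolate very low Hb: a shift from 14 to 13 g/dl counts as much as one from 8 to 7. The linear model uses the low values but does not study severity as such. The pooling of mild with severe anemia is thus a limit of the planned outcome that the companion analysis only partly relieves.

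Lastly, a condensed article may leave supportive analyses to a fuller document, so their absence is no defect in itself. What remains is a choice the article does state: its factor analysis is built on the yes/no outcome alone, although Hb on its own scale is available.

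**Conclusion.** The point holds as a loss of efficiency, not as an error. The loss is about 36% to 50% over the protocol's prevalence range if Hb is roughly normal, the shift is small and uniform, and the outcome is a pure Hb cut. It should not be quoted as a fact about this population: other shapes give anything from near zero to over 60%, and the hematocrit limb of the definition is left out of the calculation. Under the normal assumption, a shift that Hb itself would detect with 80% power is detected with about 49% to 60%. This is a cheap improvement; it does not put the validity of the primary analysis in doubt.

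**What to change.** In the Data analysis section, keep WHO-defined anemia with logistic regression as the primary analysis. Add a prespecified companion: linear regression of venous (complete blood count) Hb in g/dl, with robust standard errors and the same covariates as the logistic model, reporting adjusted mean differences with 95% confidence intervals. Name the venous value explicitly, because Hb is measured by two methods.

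The change takes a few sentences and needs no new data, visits or samples. The cost is that results appear on two effect scales, so the text should say in advance that the odds ratios are primary and the mean differences supportive.

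Suggested wording: *As a prespecified companion to the logistic model, venous Hb (g/dl) will be analysed by linear regression with robust standard errors and the same covariates; adjusted mean differences with 95% confidence intervals will be reported.*
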